# STUDY DESIGN

This is a double-blind randomized 5 year study with two arms. Patients who are scheduled for primary OLGB surgery are eligible when during the surgery total small bowel length can be measured and when they are able to swallow the Fitforme WLS primo multivitamin capsule. Patients will be allocated to one of the two surgical treatment arms by randomization at the beginning of the operation. Only the operating surgeon is aware of the allocation and will document total small bowel length, treatment allocation and BP-length in a coded database. Both the TSBL and the length of the BP-limb will not be documented in the patient file. The investigators and the patient will not be informed on the BP-limb length during the study.

Patients with a small bowel that could not be measured during surgery will be treated according to the current daily practice and will not enter the study.

# STUDY POPULATION

## Population : patients from the Centrum Obesity North-Netherlands (CON), who comply with the IFSO criteria during a multidisciplinary screening and have chosen to have a primary mini-GB (OLGB) and are willing to participate.

## Inclusion criteria

In order to be eligible to participate in this study, a subject must meet the following criteria:

- Age between 18 and 65
- BMI > 40 kg/m^2^ or
- BMI > 35 kg/m^2^  with co-morbidity : diabetes, hypertension, OSAS, arthrosis
- Willing to participate with written informed consent before start of the surgery
- A completely measured total small bowel during surgery
- No pre-operative deficiencies of vit B_12_, vit D and iron, measured with ferritin
- No use of extra (multi-)vitamin supplements with exception of vit D max 800 IU/day
- Able to swallow the multivitamin FFM WLS primo (tested before surgery)

## Exclusion criteria

A potential subject who meets any of the following criteria will be excluded from participation in this study:

- BMI > 50 Kg/m^2^
- Known gastro-intestinal disease or history of gastro-intestinal disease, e.g. celiac disease, inflammatory bowel disease
- Known addiction behaviour
- Intolerance to Fitforme Primo multivitamin
- Pregnancy planning within the first two years after surgery
- Renal or hepatic insufficiency
- Former abdominal surgery unabling the measurement of the small bowel during laparoscopic surgery
- Parenteral use of vit B_12_

## Sample size calculation

The null hypothesis in the study is as follows : the percentage TWL at five years in both groups is not different with a mean of 35. The alternative hypothesis is that the mean of the absolute difference in TWL in the experimental group is 5% more than the standard group (40% and 35% respectively).

For the evaluation of the primary endpoint of the percent total weight loss (%TWL) at five years, a sample size of 2x 92 will achieve 80% power to detect a (absolute) difference of -5.0% between the null hypothesis ( both group means of %TWL are 35.0) and the alternative hypothesis (mean of experimental group is a %TWL of 40.0) with estimated group standard deviations of 12.0 and 12.0 and with a significance level (alpha) of 0.05 using a two-sided two-sample t-test.

In case of a reduced standard deviation in the active treatment group of 9.0, the power achieved is 88.8%.

With an expected maximum drop-out due to conversion of OAGB to RYGB of 15% the sample size is 92 plus 14 = 106 patients in each group, leading to a total of 212 participants in the study.

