## Withdrawal of individual subjects

Subjects can leave the study at any time for any reason if they wish to do so without any consequences. The investigator can decide to withdraw a subject from the study for urgent medical reasons.

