**8.2.3 Suspected unexpected serious adverse reactions (SUSARs)**

Conversion of the OLGB to a RYGB due to untreatable biliary reflux is expected to occur in 5-10% of patients. They will be reported through the web portal *ToetsingOnline*

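### The drop-out allowance is added as 15% of 92 and assigned to conversion alone, so at the protocol's own 15% maximum 106 per arm leaves 90 evaluable and 79.4% power, slightly below the stated 80%

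*Protocol*

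**What the plan says.** All references are to the Protocol.

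- **Sample size calculation (4.4), target.** The alternative is that "the mean of the absolute difference in TWL in the experimental group is 5% more than the standard group (40% and 35% respectively"), "with estimated group standard deviations of 12.0 and 12.0", "with a significance level (alpha) of 0.05 using a two-sided two-sample t-test". On these inputs "a sample size of 2x 92 will achieve 80% power". A second scenario follows: "In case of a reduced standard deviation in the active treatment group of 9.0, the power achieved is 88.8"%.
- **Sample size calculation (4.4), allowance.** "With an expected maximum drop-out due to conversion of OAGB to RYGB of 15% the sample size is 92 plus 14 = 106" per group, 212 in total.
- **Section 8.2.3 (SUSARs).** "Conversion of the OLGB to a RYGB due to untreatable biliary reflux is expected to occur in 5-10% of patients".
- **Withdrawal of individual subjects (7.4).** "Subjects can leave the study at any time for any reason if they wish to do so without any consequences". No rate is given for such departures.
- **Specific criteria for withdrawal.** Converted patients are withdrawn and not replaced. They are to be analysed by intention to treat, but only their data up to conversion are used.
- **Replacement of individual subjects (7.5).** Patients withdrawn in the first 30 days are replaced, as are those who cannot swallow the capsule or whose bowel cannot be measured.
- **Handling of missing data (section 9).** Only observed values are analysed; nothing is imputed.

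**The concern.** Two things are wrong with the allowance.

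First, a drop-out allowance has to be taken from the number enrolled. To have n evaluable after losing a fraction d, one enrols n/(1 - d). The protocol enrols n(1 + d), which always falls short. At its own drop-out figure, the planned size does not return the 92 it was built to protect.

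Second, the 15% is attributed to a single cause. The primary endpoint is measured at 5 years, patients may leave at any time, only losses in the first 30 days are replaced, and a missing 5-year weight simply drops out of the t-test. Loss for reasons other than conversion therefore also reduces the evaluable number, and as written nothing is set aside for it.

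At stake is whether the stated power describes the trial as planned. The first defect is a small numerical error. The second could cost more, but its size depends on an attrition rate that the protocol does not give.

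**Working it through.** **Inputs (Sample size calculation):** difference 5 points of %TWL; SD 12 in both arms, or 12 and 9; two-sided alpha 0.05; 92 evaluable per arm; 15% drop-out; 106 enrolled per arm. Conversion of 5-10% comes from section 8.2.3. Other loss is not given, so 10% and 20% are used as assumptions.

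**Formula.** Power is the probability that a noncentral t exceeds its two-sided 5% critical value, with noncentrality 5/√[(s₁² + s₂²)/n] and 2n - 2 degrees of freedom (Satterthwaite degrees of freedom when the SDs differ).

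**1. The protocol's own figures reproduce.**
- n = 92, SD 12/12: noncentrality 5/√(288/92) = 2.826; power 80.3%. At n = 91 power is 79.8%, so 92 is the smallest n that reaches 80%.
- n = 92, SD 12/9: noncentrality 5/√(225/92) = 3.197; power 88.9% (stated 88.8%).
- Allowance: 92 × 1.15 = 105.8, rounded up to 106. This is the only route that gives 106.

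**2. The allowance as it should be taken.**
- 92/(1 - 0.15) = 108.2, so 109 per arm and 218 in total: 3 more per arm, 6 more overall.
- 106 × 0.85 = 90.1 evaluable per arm. Power is 79.4% at SD 12/12 and 88.2% at SD 12/9.
- Largest total loss at which 106 still leaves 92: 1 - 92/106 = 13.2%.

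**3. Conversion at the rate expected in section 8.2.3, no other loss.**
- 5%: 106 × 0.95 = 100.7 per arm; power 83.7%.
- 10%: 106 × 0.90 = 95.4 per arm; power 81.7%.
- Room left for other loss before falling below 92: 1 - 92/100.7 = 8.6% of the remaining patients after 5% conversion, and 1 - 92/95.4 = 3.6% after 10%.

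**4. Conversion plus other loss over five years (other loss assumed; SD 12/12).**

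| Conversion | Other loss | Evaluable per arm | Power |
| --- | --- | --- | --- |
| 5% | 10% | 90.6 | 79.7% |
| 10% | 10% | 106 × 0.90 × 0.90 = 85.9 | 77.5% |
| 10% | 20% | 106 × 0.90 × 0.80 = 76.3 | 72.5% |
| 15% | 10% | 106 × 0.85 × 0.90 = 81.1 | 75.1% |

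**5. Power by total loss from all causes, 106 per arm enrolled.**

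| Total loss | Evaluable per arm | SD 12/12 | SD 12/9 |
| --- | --- | --- | --- |
| 15% | 90.1 | 79.4% | 88.2% |
| 20% | 84.8 | 77.0% | 86.2% |
| 25% | 79.5 | 74.2% | 84.0% |
| 30% | 74.2 | 71.3% | 81.4% |

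**The case against.** The strongest case on the other side has five parts.

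- **The slip is tiny.** It costs 3 patients per arm and 0.9 points of power (80.3% to 79.4%), and no design decision turns on it. This stands.
- **15% is called a maximum.** At the expected 5-10% conversion with no other loss, 106 does keep more than 92 and more than 80% power. This stands. A reader might infer that the trial is underpowered, or that 106 cannot deliver 92; the documents do not support that. It follows only at the 15% maximum, or if other loss carries the total above 13.2%.
- **The two conversion figures need not conflict.** One is a maximum for conversion with no cause named; the other is an expectation for conversion due to biliary reflux. A reader might call this a contradiction, but the two can hold together. What is missing is a statement of how they relate and whether the gap between them is meant for other losses.
- **Early losses are replaced.** Withdrawals in the first 30 days do not use up the allowance. This is right, but it leaves nearly five years of follow-up uncovered.
- **The SD may be conservative.** The Introduction cites SDs for total weight loss of up to 8.5%, without a time point, against the 12 used for planning. With 10% conversion and an assumed 20% other loss (76.3 per arm), power is 72.5% at SD 12/12, 82.4% at 12/9 and 95% at 8.5/8.5. So a loss that breaks the 80% claim at SD 12/12 need not break it at a smaller SD. The headline 80% is nevertheless stated for SD 12/12 and should be right on those terms.

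**Conclusion.** The point holds in a limited form. The inflation method is wrong, and the stated size and power do not fit together at the protocol's own maximum drop-out: 90 evaluable per arm and 79.4%, not 92 and 80%. This part uses only the protocol's figures and is minor in size.

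The attribution of the whole 15% to conversion is the more useful correction, because the power statement then covers only one source of loss under an observed-values-only analysis. How much this costs cannot be read from the protocol: the 77.5% for 10% conversion plus 10% other loss rests on an assumed attrition rate and on SD 12 in both arms.

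It might also be inferred that no extra patients would ever be needed because converted patients could supply a 5-year weight. The withdrawal criteria do not support that as written: they invoke intention to treat but use these patients' data only up to conversion.

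**What to change.** Keep 212 and restate the last paragraph of the Sample size calculation along these lines: *106 patients per arm will be enrolled. With a maximum total loss of the 5-year weight of 15% from all causes, of which conversion is expected to account for 5-10%, 90 per arm are evaluable and power is 79% (88% if the active-arm SD is 9). At 20%, 25% and 30% total loss, power is about 77%, 74% and 71% with SD 12 in both arms.*

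If the sponsor prefers to hold 92 evaluable at 15% loss, the figure is 109 per arm, 218 in total.

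Give no assurance that further patients are unnecessary unless the Specific criteria for withdrawal are first reconciled with their own intention-to-treat statement, so that 5-year weights measured after conversion enter the primary analysis.

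Cost: one rewritten paragraph, and a stated power slightly less favourable than 80%. Using weights after conversion would need a further protocol change.

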# TREATMENT OF SUBJECTS

Patients will be randomly allocated to one of the two treatment arms :

- 1. A standard BP-limb length of 150 cm
- 2. A BP-limb length depending on total small bowel length (TSBL) measured during the surgical procedure :
- TSBL : < 500 cm : 150 cm
- TSBL : 500-700 cm : 180 cm
- TSBL : > 700 cm : 210 cm

## Summary of findings from non-clinical studies

In diabetic rats long limb duodenal-jejuno-bypass (DJB) results in more weight loss than standard DJB (Zhang). No other studies are available.

## Summary of findings from clinical studies

In RYGB surgery studies have suggested that the length of the common channel can influence the outcome of weight loss, however no studies have been performed using the total small bowel length as a criterion for length of bypass, neither in RYGB nor in OLGB.

Adjusting of BP-limb length based on the initial BMI in OLGB has been done resulting in more weight loss with more BP-length however with also more vitamin and micronutrient deficiencies (2)

##

## Summary of known and potential risks and benefits

Measuring total small bowel length induces a slightly increase in risk of damaging the bowel compared to just measuring the length of the BP-limb. Surgeons are experienced in measuring bowel length in daily practice. This measurement will increase time of surgery with on average 10 minutes.

In OLGB surgery surgeons use BP-limb lengths varying between 150 - 250 cm based on personal experience. The different lengths in our study are within these measures. Surgical risks are not higher when BP-limb length is increased. Potential risks are of course to much or to little weight loss and more than expected deficiencies of vitamins and micronutrients.

Potential benefits are a better outcome of weight reduction compared to current usual care without increase in vitamin and/or micronutrient deficiencies.

# NON-INVESTIGATIONAL PRODUCT

## Name and description of non-investigational product(s)

Fitforme WSL Primo is a multivitamin and mineral containing product with a content that is especially developed for patients after OLGB. To increase compliance, it is given as a once daily dose.

## Summary of findings from non-clinical studies

Not available

## Summary of findings from clinical studies

A RCT comparing WLS Primo to conventional multivitamin supplements is currently underway (Prager et.al).

## Summary of known and potential risks and benefits

There are no known risks involved in multivitamin suppletion with the preparation used. Especially, vitamin A, B1 and vitamin D are within the range defined for safe use. Benefits are the prevention of development of vitamin and mineral deficiencies

## Description and justification of route of administration and dosage

The advised dose is one capsule once daily, orally administrated.

## Dosages, dosage modifications and method of administration

N.a.

## Preparation and labelling of Non Investigational Medicinal Product

FitForMe WSL Primo will be delivered by the regular manufacturer and distributed within their own packaging by the research team.

## Drug accountability

Each patient will be given a standard amount of the multivitamin, for the time to the next visit plus 30 extra days. They are advised to bring back all the multivitamin capsules left as well as the residual empty blisters and boxes at the day of the visit in which their number of pills are filled out to the amount for the next period plus for 30 days extra. By counting the left over pills and substracting them from the number handed out in the former visit accountability can be checked.

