## Study procedures

A standard operation protocol for OLGB will be used in all patients. The pouch will be made with the help of a linear stapler. At first, the stomach will be transected horizontally at the junction of the corpus and antrum at the level of crow’s foot. A small pouch is made with help of a calibration sonde of 34 French, the pouch is finished near the angle of His. Then the total limb length is measured. With a succesfull TSBL measurement the OR nurse will open the envelop and the allocated procedure will be communicated to the surgeon. Based on the randomization outcome biliopancreatic limb length is measured. In case the measurement of the total limb length does not succeed, standard limb length of 150 cm is performed. An antecolic, retrogastric anastomosis is performed by liniar stapling and the remaining defect is closed by V-loc. An anti-reflux stitch is performed. Integrity of the anastomoses is checked by methylene-blue-test and in case of leakage, extra sutures will be applied. The mesenterial defect of Peterson will be closed as far as possible by endo hernia stapling or unresolvable V-loc.

The extra measurements of limb length will take less than ten minutes of time. In patients allocated to standard treatment the surgeon will construct a BP-limb of 150 cm. In patients allocated to the adjustment length, the length of the BP-limb will depend on the total small bowel length : < 500 cm : 150 BP; 500-700 cm : 180 BP and > 700 cm : 210 BP.

On leave of the hospital the patients will be provided with Fitforme WSL Primo multivitamin capsules for the following period and will be instructed to use one capsule once daily.

Follow-up will take place in accordance with usual care, i.e. after 1,6,12 and 24 months and yearly up till 5 years. Extra visits will be at 18,30,42 and 54 months for compliance check and distribution of FFM multivitamins.

Weight measurements and blood samples will be taken in accordance with the standard protocol of follow-up after bariatric surgery in our institute added with 20 ml for selenium and copper measurements and future lab tests at 1,3 and 5 years.

Data from 6,12 and 24 months and every year thereafter up to five years after surgery will be anonymously collected in a database.

At each visit standard care includes :

- inquiry after well being and complaints, side effects, adverse events
- documenting current medication use, both regular and over-the-counter, and when applicable CPAP use

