- inquiring after co-morbidities
- measurement of body weight, blood pressure and pulse
- drawing of blood samples for routine post operative care including :

CRP, hemoglobin, WBC, thrombocytes, sodium, potassium, creatinin, BUN, ASAT, ALAT, alkaline phosphatase, yGT, HbA1c, glucose, calcium, magnesium, phosphate, albumin, vit B_1_, vit B_6_, vit B_12_, folic acid, ferritin, vit A, vit D, Zinc

- Scheduling a new appointment

If the patient forgot to bring along a recent overview of current medication from their own pharmacy , the actual medication use will be requested from the local pharmacy.

Extra effort for the patient in the study includes :

- Bringing along a written overview of current medication from the local pharmacy to the appointment.
- Bringing back all used and non-used blisters and boxes for counting of compliance of the use of the FitForMe WLS primo pills
- filling in the DSS questionnaire
- filling in the RAND 36 questionnaire
- drawing of 20 ml of extra blood during the venepuncture for selenium, copper and storage for later investigations at 1,3 and 5 years
- Visits at 18, 30,42, and 54 months for counting left over pills and distributing new ones for the forthcoming 6 months

All patients will be treated with 800 IU vitamin D and 500 mg Calcium in a combination pill as part of standard care.

In case of deficiencies of vitamins or micronutrients they will be substituted according to standard care.

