## For qualitative parameters (categorical or ordered), frequency counts and percentages of each category will be calculated by treatment group. Percentages will be reported up to 1 decimal place.

## Primary study parameter(s)

The primary null hypothesis for this study is that there is no significant difference in the mean change in the percent of total weight loss (%TWL) at five years, between patients treated with a TSBL adjusted BP limb length (active group) versus patients treated with a standard BP limb length of 150 cm (control group).

In addition to the descriptive statistics (see the above section : Patient demographics other baseline characteristics), the two treatment strategy groups will be compared using two-sample T-test if parameter is normally distributed. Visual inspection of the distribution, as well as the Shapiro-Wilk test for normality, will used to assess normality. Unless equality of variance between groups is established, the Satterthwaite method for t-statistics and 95% confidence intervals will be used. If data is skewedly distributed, a Mann-Whitney U-test (Wilcoxon two-sample test) will be applied. For the difference in medians, the Hodges-Lehmann estimate will be used with distribution-free 95% confidence intervals.

In addition to the above mentioned analyses, the homogeneity of treatment effect over different strata of patients will be evaluated. In this, differences in treatment effect over separate strata of potentially relevant factors (e.g. gender, baseline BMI, co-morbidities, compliance, etc) will be evaluated. A multivariable model will be used to formally establish homogeneity, i.e. the absence of effect modification for the potentially relevant factors, separately.

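### Section 9.1 lists compliance, which arises after randomisation, as an effect-modification factor for the primary %TWL effect, and the capsule count behind it is ambiguously defined

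*Protocol*

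**What the plan says.** **Analysis.** After the two-sample comparison of %TWL, Protocol section 9.1 adds an evaluation of whether the treatment effect is the same over strata of "potentially relevant factors (e.g. gender, baseline BMI, co-morbidities, compliance, etc". A multivariable model is to confirm, factor by factor, that effect modification is absent.

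**Supply.** Section 6.5 states: "The advised dose is one capsule once daily, orally administrated". Section 6.8 states: "Each patient will be given a standard amount of the multivitamin, for the time to the next visit plus 30 extra days". Left-over capsules come back at the visit, at which "their number of pills are filled out to the amount for the next period plus for 30 days extra".

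**Count.** Section 6.8 continues: "By counting the left over pills and substracting them from the number handed out in the former visit accountability can be checked".

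**Visits.** Section 7.3 (Study procedures) sets usual-care visits "after 1,6,12 and 24 months and yearly up till 5 years" and adds: "Extra visits will be at 18,30,42 and 54 months for compliance check and distribution of FFM multivitamins". It describes the extra visits as serving for "counting left over pills and distributing new ones for the forthcoming 6 months".

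The protocol describes no other measure of compliance. Section 9.1 does not itself refer to the capsule count.

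**The concern.** Gender and baseline BMI are fixed before allocation, so randomisation still balances the arms, in expectation, within their strata. Compliance is different. The envelope is opened during surgery, and the capsules for daily use are supplied on discharge, so every compliance value is formed after allocation and over the same five years as the outcome. Section 9.1 treats the two kinds of factor alike.

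If limb length affects bowel habit or nutrient status, it may also affect who keeps taking a daily capsule and who keeps attending. Compliers in one arm would then be a different kind of patient from compliers in the other. A difference in effect between compliance strata could reflect that selection, and a lack of difference could hide a real one.

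A second, smaller matter is the variable itself. Section 6.8 runs a top-up system, but its subtraction never mentions the capsules carried over.

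**Working it through.** **A. Compliance as a factor (no arithmetic applies)**

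1. *Timing.* Sections 7.2 and 7.3 place allocation in the operation, after small-bowel measurement. Capsule-taking starts at discharge. The swallowing test before surgery decides eligibility and is not a compliance measure.
2. *Route from arm to compliance.* Bowel movements and deficiencies are secondary outcomes to be compared between arms, and the risk summary in the treatment section names more deficiencies than expected as a potential risk. The design therefore allows the arms to differ in things that can change capsule-taking.
3. *Who is observed.* The count needs a visit and returned packs. The missing-data paragraph in section 9 leaves missing values missing, so patients without a count fall out of the strata.
4. *Result.* Conditioning on compliance selects on a variable that allocation may affect. The within-stratum contrasts lose the protection of randomisation even if the count is perfect.

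**B. The capsule count**

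The protocol states no capsule total or compliance percentage, so there is no figure to reproduce.

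Inputs: one capsule per day (6.5); target stock D + 30, where D is days to the next visit (6.8); six-month intervals from month 6 on (7.3). Assumptions: D = 183 days (range 180 to 184), and D as the denominator.

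Target stock: S = 183 + 30 = 213. Let L be the left-overs at a count and T the newly dispensed top-up, T = S − previous L.

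*Whole-stock reading (number handed out = S); use = S − L:*
- Full taker: 213 − 30 = 183, and 183/183 = 100%.
- Patient who takes none: 213 − 213 = 0.

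*Top-up reading (number handed out = T); use = T − L:*
- Full taker: T = 213 − 30 = 183 and L = 30, so 183 − 30 = 153 and 153/183 = 83.6% (83.3% to 83.7% for D = 180 to 184).
- Full taker who then stops: at the next count T = 183 and L = 213, giving −30 (−16.4%). At the one after, T = 0 and L = 213, giving −213 (−116.4%).
- Steady adherence f: L = D + 30 − fD and T = fD, so (T − L)/D = 2f − 1 − 30/D. With D = 183, f = 0.9 reads 63.6% and f = 0.8 reads 43.6%. The result is negative below f = (1 + 30/183)/2 = 58.2%.
- Half use followed by full use, with D = 182: S = 212, L = 212 − 91 = 121, T = 91, then L = 30. The count gives (91 − 30)/182 = 33.5% where the truth is 100%.

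The first interval has no carry-over and is right on either reading. If stock is also counted and refilled at month 1, a full taker's month 1 to 6 interval (152 days) would read (152 − 30)/152 = 80.3% on the top-up reading.

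*With carry-over counted* (previous left-overs + top-up − current left-overs): full taker 30 + 183 − 30 = 183, or 100%; later count after stopping, 213 + 0 − 213 = 0.

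**The case against.** **On the factor.** Compliance is one example in an open list, within an evaluation that is additional to the main analysis. The multivitamin goes to both arms and is not the randomised treatment. Patients and follow-up staff are blinded, so knowledge of the arm should not drive capsule-taking. All of this stands and limits the point to an exploratory analysis. It does not remove the point: blinding does not stop side effects from changing behaviour, and section 9.1 draws no line between baseline and post-randomisation factors.

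**On the count.** A reader might infer that section 6.8 contains a plain arithmetic error under which full takers are recorded at about 84% and stoppers below zero. The text does not support that. The section opens by saying that each patient is given a standard amount equal to the interval plus 30 days. If that amount is the number handed out, the subtraction is exact. The top-up reading is also open, because section 7.3 speaks of handing out new capsules, but nothing settles the choice. The protocol also sets no denominator or cut-off, so nobody is classed as non-compliant by any rule in it. Negative counts would be noticed, and true use can be recovered if dispensed and returned numbers are both logged.

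It is also true that, for patients with steady adherence, the top-up reading preserves their order. That fails once adherence changes: the patient above who moves from half to full use reads 33.5%, below the 43.5% of a steady 80% taker at the same D (2 × 0.8 − 1 − 30/182).

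**Conclusion.** The point holds as a caution on section 9.1: effects within compliance strata are not randomised comparisons, and compliance does not belong with baseline factors in a check for effect modification. This does not depend on how the capsules are counted. The direction and size of any bias cannot be worked out from the protocol. That section 9.1 means the capsule count is an inference, resting on its being the only compliance measure described.

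A reader might go further and infer that the primary result is at risk. It is not: the two-sample comparison of %TWL is not stratified by compliance, and the sample size does not depend on it.

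The counting rule is a minor ambiguity. There is no error on the whole-stock reading. On the top-up reading a full taker reads about 84% in six-month intervals, and a full taker who stops reads negative from the next count. Both figures rest on the assumed interval length, and the percentage also on the assumed denominator. A patient who never takes the capsules reads zero, not negative, at the first count.

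**What to change.** 1. **Section 9.1.** Limit the effect-modification factors to characteristics measured before randomisation, such as gender, baseline BMI and co-morbidities at baseline. Remove compliance, and report it descriptively by allocated arm with the number of patients who have a count at each visit.
2. **Section 6.8.** State that capsules used in an interval = capsules carried over + capsules newly handed out at the previous visit − capsules returned, divided by the days in the interval. Have the newly dispensed and the returned numbers logged separately at each visit.

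Cost: two wording changes and the loss of one exploratory subgroup. No new visit or measurement is needed.
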